## Abstract

**Background:**

Children born with a cleft palate with or without a cleft lip (CP/L) are at increased risk for delayed language development and speech sound disorders. Enhanced Milieu Teaching with Phonological Emphasis (EMT+PE) is a recommended naturalistic intervention for toddlers with CP/L. The parents’ role in providing naturalistic interventions is critical and they need training based on learning principles to implement these interventions. Telepractice is an appropriate method for training parents and children with various speech-related disorders.

**Objective:**

This study aims to determine and compare the effectiveness of telepractice and the parent-implemented EMT+PE intervention on language and speech measures in toddlers with CP/L with usual interventions and determine the effectiveness maintenance of the intervention.

**Methods:**

A randomized controlled trial (RCT) will assess the efficacy of telepractice and the parent-implemented EMT+PE intervention in enhancing speech and language measures in toddlers with CP/L. Eligible participants will be randomly assigned to one of 2 groups: the conventional intervention group and the EMT+PE intervention group. Participants’ speech and language measures will be evaluated remotely by trained raters before and after the intervention and 2 months after the intervention. Parents of participants in the intervention group will receive 3 months of training in speech and language supportive strategies from trained therapists using telehealth fidelity scales. Parents of participants in the control group will receive the conventional speech and language intervention by cleft team therapists. Study outcomes will include language variables (mean length of utterance) and speech production variables (percent correct consonants).

**Results:**

The protocol was approved by the Research Ethics Committee of the University of Social Welfare and Rehabilitation Sciences in February 2022. The selection process of participants, as well as training therapists and raters, commenced in January 2022, the therapy and follow-up period ended in June 2023, and pre- and postintervention assessments have been conducted. Data analysis is ongoing, and we expect to publish our results by the summer of 2024. Funding is yet to be received.

**Conclusions:**

The results of this study may help us develop a speech and language intervention with a different delivery model for toddlers with CP/L, and the cleft team care can use these results in service delivery. Consistent with our hypothesis, speech and language measures are expected to improve.

**International Registered Report Identifier (IRRID):**

DERR1-10.2196/54426

## Introduction

### Background

Cleft palate with or without cleft lip (CP/L) frequently leads to difficulties with speech and language [1-5]. Previous studies have reported that children with CP/L have limited consonant inventory, which leads to decreased expressive vocabularies [6-8]. Thus, trained and experienced speech-language pathologists (SLPs) in cleft and craniofacial teams often provide speech-language therapy services for these children. Team-based cleft care for this population follows particular intervention protocols. However, due to limited cleft teams in some countries or regions, especially in low-income and transitional countries, and the long distance between the cleft teams and families’ residences, many of these children are unable to receive appropriate speech-language therapy services. Parent training and telepractice therapy sessions could help fill this gap [9-12].

Training and coaching for parent-implemented interventions have been known as practical methods to prevent or improve speech-language disorders in children [9-14]. Parents are considered the first teachers of their children’s speech and language development since they spend considerable time with their children in a natural environment, which provides them many opportunities to teach their children through daily routines. Intervention approaches in speech-language pathology have highlighted the crucial role of parents in these approaches. Parents are trained to use supportive language and speech strategies while interacting with their children [14]. Training strategies parents use in a child’s environment also facilitate the transfer of therapy from clinical settings to the child’s natural environment [15-17]. A systematic review of 18 studies [18] analyzing parent-implemented interventions revealed that parents who received training increased their responsiveness, usage of language models, and rate of communication with their children—in addition to the use of language-supportive strategies—had positive impacts on expressive language in preschool children with or without language impairments.

Language and motor intervention approaches have been used for children with CP/L. A systematic review [19] comparing the benefits of linguistic and phonological versus motor phonetics approaches revealed that although all the studies reported significant findings, they did not report a more effective intervention approach. Other studies [8] showed that both approaches improved consonant inventory; however, the linguistic and phonological approach was more effective in improving speech outcomes. Most of these studies have been conducted with children older than 4 years. It seems that the naturalistic-based approach is more effective in and applicable to younger children [20]. Enhanced Milieu Teaching (EMT) is one of the approaches of the naturalistic approach. It is a conversation-based naturalistic model for early language intervention that uses children’s interests and initiations as opportunities to model and encourage language use in daily routines [15]. EMT with Phonological Emphasis (EMT+PE) extends the prompting strategies of EMT to include Phonological Emphasis (PE). PE or speech recasts are a subset of recasts that target correct phonological production in response to the child’s incorrect productions [5,11,12,21]. Studies have reported positive effects of EMT+PE on language and speech outcomes including the percentage of correct consonants (PCC), consonant inventory, word production speed, compensatory errors, expressive vocabulary, and receptive language [5,21,22]. EMT+PE delivery methods are flexible for children with CP/L. Two pilot studies have demonstrated the effectiveness of the EMT+PE intervention via telepractice [11,12].

Telepractice refers to services delivered over long distances using videoconferencing or other technologies. Also, it is a service delivery model for different purposes in specific populations with communication disorders [13,23]. Telepractice is used to train parents in parent-implemented approaches [11,12,24]. Parent training via telepractice is implemented through different media such as videoconferences, YouTube videos, and web-based modules. The type of media for service delivery depends on the media facilities [24,25]. Previous research has indicated that treatment outcomes are comparable for both in-person and telepractice service delivery, and these methods are used as alternatives or as a hybrid approach [26].

The prevalence of cleft lip and palate (CLP) in Iran has been reported as 1.24 per 1000 births, with an incidence rate of 1 in 1000 births [27,28] There are 6 active cleft teams in Iran, all located in the center of major provinces. Iran, with a population of over 80 million individuals, of which 26% live in rural areas and 74% in cities, most families with a child with CLP are likely to face significant challenges in accessing team services or may not have the opportunity to use them due to their living conditions. According to various studies [26,29], telepractice service delivery can largely address the problems of health care services and provide timely access to services for children and families; therefore, our objective is to develop a protocol to evaluate the effect of a parent-based telepractice EMT+PE intervention on speech and language outcomes in Persian-speaking toddlers with nonsyndromic cleft palate, and compare this intervention to conventional, usual-care interventions.

### Aims

#### Primary Objectives

Our primary objective is to determine the effectiveness of a parent-based telepractice EMT+PE intervention on language and speech outcomes in toddlers with CP/L.

#### Secondary Objectives

Our secondary objectives are to compare the effectiveness of this parent-based telepractice EMT+PE intervention with usual-care interventions and determine the effectiveness of the intervention in the follow-up period.

## Methods

### Study Design

This is a single-blind, 2-arm, parallel randomized controlled trial (RCT).

### Study Population and Setting

The study will enroll 32 children with different types of oral cleft including unilateral cleft lip and palate, bilateral cleft lip and palate, and isolated cleft palate (Figure 1).

Participants will be recruited through local cleft palate teams in 3 major provinces (Esfahan, Tehran, and Shiraz), social media support groups, and local speech and language centers. All child-parent dyads will be required to meet the inclusion criteria.

**Figure 1 figure1:**
[figure not shown]
CONSORT (Consolidated Standards of Reporting Trials) flowchart showing the flow of participants in both groups.

### Inclusion and Exclusion Criteria

Eligible participants including children, their parents, and SLPs will be recruited through a rigorous review of the literature in this field [4,11,12,21].

#### Inclusion Criteria

##### Children

The inclusion criteria for children are as follows: (1) Persian-speaking children with CP/L aged between 18 and 36 months before the intervention, (2) lack of a diagnosis of a syndrome by a geneticist and by referring medical records to cleft care teams, (3) undergoing primary palate repair by the age of 15 months, (4) absence of sensorineural hearing loss or a sound field hearing threshold greater than 30 dB HL (decibels in hearing level), (5) preintervention assessment of typically developing children wherein scores on the Age and Stages Questionnaire in all domains (communication, fine motor, gross motor, personal and social, and problem-solving skills) are within the normal range (±1 SD from the cutoff points in each domain), (6) the child’s sufficient joint attention with the parent during the collection of play-based language samples, (7) at least 1 type of compensatory error throughout the speech sample, and (8) the child can produce at least 5 different words as measured using the Macarthur-Bates Communicative Development Inventory (MCDI).

##### Parents

The inclusion criteria for parents are as follows: (1) having literacy skills at least at the level of elementary school education, (2) being interested in participating in the assessment and telepractice training sessions, and (3) being able to use a cell phone containing apps that will be used in the intervention.

##### SLPs

The inclusion criteria for SLPs are as follows: (1) having at least 5 years of experience in providing treatment approaches for children with speech-language disorders, (2) not currently delivering EMT+PE and not previously trained in the interventional approach, and (3) having experience in treating children with various speech-language disorders via telepractice.

#### Exclusion Criteria

##### Children

Children will be excluded from the study if they (1) are bilingual or do not speak Persian, (2) have other dysmorphic features that affect speech (fistula in the palate), (3) have been receiving either therapy in the last 6 months or speech therapy in private clinics, or (4) are participating in another research study involving an intervention or multiple assessments.

##### Parents

Parents will be excluded from the study if they are (1) unable to properly implement speech- and language-supportive strategies or (2) unwilling to continue with the intervention process.

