### Randomization and Blinding

#### Overview

After preassessments, participants will be allocated to either of 2 intervention groups to eliminate selection bias and control for any extraneous variables: EMT+PE or the usual-care intervention. Block randomized trials will be conducted for each age group using the blockrand package in R software (version 4.1.3; The R Foundation). Randomization will be based on age (3 age groups) and the 2 interventions. The flow of participants through the study is illustrated using the CONSORT (Consolidated Standards of Reporting Trials) flowchart in Figure 1.

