#### Usual-Care Intervention

Children assigned to the usual-care intervention (control) group will be assessed twice before and after the 3-month intervention. If they are not, they will be enrolled in cleft teams. They will receive speech and language therapy there in accordance with a specific protocol. Regular evaluations administrated every 3-6 months, are part of the usual speech and language intervention for children aged up to 3 years undergoing team care. Based on each child’s evaluation, early counseling is provided to parents in person or remotely. Parents are expected to apply the recommendations provided until the next visit. The EMT+PE will not be administered to participants in the control group throughout the experimental intervention period.

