#### Fidelity of Implementation for Parents

Parents’ ability to implement the trained EMT+PE strategies with procedural fidelity will be determined through formative visual analysis based on established learning criteria. To ensure fidelity, therapists and an independent expert will assess parents’ use of each strategy during 8 monthly sessions, using a checklist. The criteria for the strategies are as follows: environment arrangement (80%), language mapping (75%), match turns (75%), expansions (50%), modeling (40%), child’s target level (50%), prompt (80%), delay (80%), and speech recast (40%). The reliability of parents’ fidelity will be measured during the intervention [12,13] (Multimedia Appendix 2).

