### Statistical Analysis

#### Analysis

The analysis will be carried out using descriptive and analytical statistics. Descriptive statistics appropriate for summarizing demographic information and assessment data will be used. Preintervention differences between groups will also be estimated. The data analysis will be carried out using the SPSS (version 19; IBM Corp). The study’s outcomes will be presented as an estimation of the difference between groups, with a 95% CI and its associated *P* value. The statistical significance level will be set at α=.05*.* We will use analysis of covariance, an efficient statistical test that provides impartial estimations of an intervention’s effects, assuming random treatment assignment; this test is more powerful than other alternative statistical strategies. We will also carry out a paired samples *t* test, which compares the means of 2 variables within a single group; it estimates the differences between the values of 2 variables for each case and tests whether their average is significantly different from 0. Additionally, data from all randomized participants will be included in the intention-to-treat analysis.

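### The parent exclusion rule can remove families after randomisation, mainly from the EMT+PE arm, and is not reconciled with the promise to analyse everyone randomised

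*Protocol article*

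**What the plan says.** Under Exclusion Criteria, the Parents section begins "Parents will be excluded from the study if they are" and gives two grounds: "unable to properly implement speech- and language-supportive strategies or (2) unwilling to continue with the intervention process". It does not say when the rule is applied, or whether the child's outcomes are still collected afterwards.

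Other sections fix the order of events:

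- **Randomization and Blinding, Overview:** "After preassessments, participants will be allocated to either of 2 intervention groups".
- **Abstract, Methods:** "Parents of participants in the intervention group will receive 3 months of training in speech and language supportive strategies".
- **Parent Training:** parent competence is judged on fidelity scales tied to the strategies that were trained.
- **Fidelity of Implementation for Parents:** parents' ability to use the strategies "will be determined through formative visual analysis based on established learning criteria", and the assessment takes place in the course of the intervention.
- **Usual-Care Intervention:** "The EMT+PE will not be administered to participants in the control group throughout the experimental intervention period". Control parents receive counselling, and "Parents are expected to apply the recommendations provided until the next visit". No fidelity check is described for them.

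The Analysis section states that "data from all randomized participants will be included in the intention-to-treat analysis".

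**The concern.** An exclusion criterion normally acts before randomisation. This one appears to depend on how parents perform once training has begun, and training is given in one arm only. A rule of that kind would take weak implementers out of EMT+PE while their counterparts in usual care, who are never tested, stay in. The arms would then no longer be comparable by randomisation.

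In a parent-implemented programme, how well parents take it up is part of the effect being estimated. A comparison without the families who struggled or stopped describes successful implementers. It does not describe the effect of offering the programme, which is what an intention-to-treat analysis is meant to give.

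**Working it through.** **1. When, and in which arm, can each ground operate?**

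| Ground | What is needed to judge it | When available | Arm |
|---|---|---|---|
| (1) Cannot implement the strategies | Training, then fidelity scoring | After allocation | EMT+PE only |
| (2) Will not continue | An intervention under way | After allocation | Nominally both, mainly EMT+PE |

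No preassessment of parents' strategy use is described. Literacy, interest in the sessions and ability to use the phone apps are already inclusion criteria for parents, so a pure screening reading would add little. For ground (2), EMT+PE parents have contact twice a week for 3 months and submit videos. Usual care consists of evaluations every 3 to 6 months with counselling. The opportunity to be unwilling to continue is therefore very unequal.

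**2. Does the planned sample size allow for removals?**

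Inputs from Intended Sample Size: variance 0.0036 (SD 0.06), difference 0.06 in PCC, 80% power, and α = 0.05 taken as two-sided.

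n per group = 2 × (1.960 + 0.842)² × 0.0036 / 0.06² = 2 × 7.85 × 1 = 15.7, rounded up to 16.

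The stated 16 per group is reproduced. Total enrolment is 32 = 2 × 16, so the design carries no allowance for removed families.

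**3. How large could the bias be?**

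The article gives neither the number of removals nor the link between fidelity and outcome, so both are assumptions. The model has 16 v 16 children, no true effect and an unadjusted two-sample t test. The 3 EMT+PE families lowest on implementation are dropped, and implementation has correlation r with the child's outcome.

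The mean of the best 13 of 16 standard normal values is 0.311 by simulation, so the bias is r × 0.311 SD. Multiplying by 0.06 gives PCC units.

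| r | Bias, SD | Bias, PCC | Two-sided type I error | Rejection in favour of EMT+PE |
|---|---|---|---|---|
| 0 | 0 | 0 | 5% | 2.5% |
| 0.3 | 0.3 × 0.311 = 0.093 | 0.006 | 5.8% | 4.3% |
| 0.5 | 0.5 × 0.311 = 0.156 | 0.009 | 7.2% | 6.2% |
| 0.7 | 0.7 × 0.311 = 0.218 | 0.013 | 9.6% | 8.9% |

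The rejection rates are simulated, and repeat runs differ by about 0.2 percentage points. At r = 0.5 the bias is 0.009 / 0.06 = 15% of the planned difference. With 1 to 4 families dropped at r = 0.5, the bias runs from 0.06 to 0.20 SD and the two-sided error from 5.4% to 8.3%.

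**The case against.** The rule stands beside ordinary entry criteria and carries no timing, so its post-randomisation effect is an inference. The fidelity review is described as formative, and nothing says that missing a fidelity threshold triggers removal. The only statement about the analysis set includes everyone randomised. If exclusion meant only the end of training, with outcomes still collected, the two sections would be compatible. This much stands: the sections are unreconciled rather than impossible to follow together. But the text says excluded from the study, and nothing says that such families are still assessed.

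A reader might also infer more than the document supports:

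- **That the rule can never touch a usual-care family.** This holds for ground (1) only. The article calls both arms intervention groups, so ground (2) can nominally reach controls.
- **That every outcome is biased towards EMT+PE.** The direction rests on an assumed positive link between implementation and outcome, and a family may also stop because the child has improved. The satisfaction survey concerns the EMT+PE programme and is not a comparison between arms.
- **That power is lost as well.** At a 1 SD difference, exact t-test power falls from 78% (16 v 16) to 73% (13 v 16) only if the 3 dropped families are a random subset. Under the model above with r = 0.5, rejection rises to about 86%, because the bias adds to the true difference. Bias and power loss cannot both be claimed from one scenario.
- **That families were in fact removed.** The article does not report any removals.

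The illustration is also unadjusted, whereas the plan is analysis of covariance.

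**Conclusion.** The rule is wrong as written. Ground (1) can act only after randomisation and only in EMT+PE. Ground (2) acts mainly there. Neither is reconciled with the stated intention-to-treat analysis. That conclusion rests on the text and needs no numerical assumption.

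The size of the effect cannot be computed from the article. With 3 removals and correlations of 0.3 to 0.7, the bias is about 0.09 to 0.22 SD and the two-sided type I error 5.8% to 9.6%. With no correlation, or no removals, there is no bias. Confidence is high in the conflict and limited for its magnitude. The point must be settled because it decides who enters the primary comparison.

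**What to change.** Reconcile the Parents exclusion section with the Analysis section. Remove the two parent criteria as grounds for leaving outcome assessment and analysis, and state that every randomised child is analysed in the allocated arm whatever the parent's fidelity or continuation. When training stops is a clinical question and stays with the investigators.

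The Results section says that therapy and follow-up ended in June 2023 and that data analysis is ongoing, so the following can still be done:

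1. Report how many families were removed under this rule, by arm and reason, including if the number is zero.
2. Include every randomised child with a post-intervention sample in the analysis of covariance.
3. Show the result without low-fidelity families only as a labelled sensitivity analysis.
4. Where a removed family has no post-intervention sample, report it as missing by arm, add a missing-data sensitivity analysis, and do not describe a set that omits it as all randomised participants.

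The cost is wording in two sections, a rerun of the analysis with the added sensitivity analyses, and a possibly less favourable estimate. Outcomes that were never collected cannot be recovered now, so for those families the fix is limited to transparent reporting and sensitivity analysis.

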##### SLPs

SLPs will be excluded from the study if they are unable to provide weekly family therapy sessions.

